## Abstract

**Background:**

Depression and dementia are major public health problems in the UK. Depression in early-stage dementia is very common and significantly reduces quality of life, speeds cognitive decline and increases functional impairment. Mindfulness-Based Cognitive Therapy (MBCT) is an effective depression prevention programme, and the National Institute for Clinical Excellence (NICE) has suggested that MBCT is a priority for implementation. Alongside this, there is emerging evidence demonstrating promising results in relation to the benefits of adapted mindfulness interventions for people with dementia, suggesting that it could be beneficial in reducing depressive symptoms and in slowing deterioration in cognitive functions such as sustained attention, distraction inhibition and task switching.

**Methods:**

The design is a single-blind randomised controlled feasibility trial. Participants with mild to moderate depression and early stages of dementia will be recruited from the participating memory services. Participants will receive either immediate or delayed access to an 8-week MBCT programme. Participants will be assessed by a blind assessor and complete cognitive and mood-related outcome measures before and after the intervention. This feasibility study will test the trial design and assess recruitment, retention, acceptability and adherence, as well as providing preliminary efficacy data.

**Discussion:**

This study will inform the design and sample size for a future full randomised controlled trial (RCT), which will be carried out to determine the effectiveness of the intervention in reducing depressive symptoms in people with early stages of dementia.

**Trial registration:**

ClinicalTrials.gov ISRCTN16382776

## Background

Depression and dementia are major widespread public health problems in the UK, with the numbers of people with dementia set to rise to 1.7 million by 2051 [1]. It is estimated that 50% of people with dementia experience some symptoms of depression, and the rate of persistence of symptoms is high [2]. Evidence suggests that the onset of depression is linked to a dementia diagnosis [3]. Comorbid depression in dementia (i) significantly reduces quality of life [4], (ii) speeds cognitive decline [5], (iii) increases functional impairment and the need for nursing home placements [6], (iv) is associated with higher mortality rates [7], (vi) increases carer stress [8] and (vii) is costly for health resources, with an increased use of expensive inpatient beds [9].

The Improving Access to Psychological Therapies (IAPT) programme has successfully rolled out services providing Cognitive Behavioural Therapy (CBT) in England [10], with good outcomes in terms of depressive symptom reduction [11]. The government has now pledged to increase access to evidence-based therapies to all patient groups, including older people and people with dementia [12]. However, there is currently little evidence for the benefit of psychological interventions for depression in people with dementia [6]. A recent meta-analysis has concluded that Mindfulness-Based Cognitive Therapy (MBCT) is an effective depression prevention programme for people without dementia, but with a history of recurrent depression [13]. In addition, the National Institute for Clinical Excellence (NICE) has suggested that MBCT is a priority for implementation. Alongside this, there is emerging evidence demonstrating promising results in relation to the benefits of adapted mindfulness interventions for people with dementia, suggesting that it could be beneficial in reducing depressive symptoms and in slowing deterioration in cognitive functions such as sustained attention, distraction inhibition and task switching [14].

Recently, evidence from an adapted mindfulness intervention feasibility study for people with dementia in care homes (*n* = 31) showed that a modified mindfulness intervention was feasible and that it led to significant improvements in quality of life [15]. There were no significant changes in mood. However, the study did not actively recruit people with depression and a third of the participants from the intervention group who were in the clinically depressed range at baseline moved out of the range at follow-up. In contrast, none of the participants in the control arm did, suggesting that the intervention should be further tailored and target people with comorbid depression and dementia.

This current study will be the first to investigate the feasibility and potential efficacy data of MBCT in people with comorbid dementia and depression, using qualitative and quantitative methods as recommended by the Medical Research Council [16].

The aim of this study is to provide evidence for the feasibility of conducting a fully powered RCT to evaluate a complex psychological intervention for depression in people with early stages of dementia. Feasibility will be evaluated in it in terms of rates of recruitment, retention and adherence to treatment protocol. The potential efficacy of the intervention will also be estimated.

## Methods/design

### Design

A single-blind randomised feasibility trial will be carried out to test the delivery of an MBCT intervention for people with mild to moderate depression and comorbid early stages of dementia. In this RCT, 50% of participants will be randomly allocated to the immediate group (IA) and will receive MBCT immediately. The remaining 50% of participants will be allocated to the delayed access control (DAC) group. Both arms will receive treatment as usual. Participants will be assessed by blinded assessors that will not be involved in the delivery of the intervention at any point. Assessors will provide explicit reminders to the participants before the assessment visit so that participants do not disclose group allocation inadvertently. The assessor will also record their impression of which arm of the trial the participants belong to and their confidence in that prediction on completion of the follow-up assessments. This will enable us to assess whether inadvertent loss of blinding leads to bias.

Alongside the running of the study, a progress evaluation will be carried out by interviewing participants taking part in the groups in order to gather qualitative information that can support and enhance the quantitative findings of the feasibility study. In order to gather in-depth data regarding people with dementia’s experience of attending a mindfulness group, participants that attended the group will be invited to a semi-structured interview after the group. Approximately 10–12 interviews with group participants and family caregivers will be conducted. Carers of participants will be invited to further examine whether potential benefits of the MBCT intervention were generalised to other areas that relate to activities of daily living such as engagement in home-based practice and improvements observed at home.

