### Carer measures

This will be conducted by the assessor in a private room in the memory clinic or in the participant’s home. The assessor will ask a member of staff or family member questions about the relevant participant’s, mood, anxiety and quality of life. The information obtained will be used in combination with the information gathered from the interview with the participant to complete the following assessments:Cornell Scale for Depression in Dementia [20]Quality of Life–Alzheimer’s Disease Scale: Carer Version [22]Rating Anxiety in Dementia (carer version) [27]

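### The non-disclosure reminder is addressed to participants only, but the blinded assessor also interviews a staff or family informant who may know the arm and whose answers enter the CSDD and RAID

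*Protocol article*

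**What the plan says.** The Design section of the protocol article calls the trial single-blind and states: "Participants will be assessed by blinded assessors that will not be involved in the delivery of the intervention at any point". It then gives one measure against disclosure at the visit: "Assessors will provide explicit reminders to the participants before the assessment visit so that participants do not disclose group allocation inadvertently". The next sentences have the assessor record, once the follow-up assessments are complete, which arm they think the participant is in and how confident they are. The stated purpose is to judge whether loss of blinding leads to bias.

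The Carer measures section adds a second source of information at the assessment: "The assessor will ask a member of staff or family member questions about the relevant" participant's mood, anxiety and quality of life. On how those answers are used, it says: "The information obtained will be used in combination with the information gathered from the interview with the participant to complete the following assessments". The assessments listed are the CSDD, the carer version of the QoL-AD and the carer version of the RAID.

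On what carers may know, the Design section says of the qualitative interviews: "Carers of participants will be invited to further examine whether potential benefits of the MBCT intervention were generalised" to daily life, including practice at home and changes noticed there.

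**The concern.** The CSDD and RAID are described under Outcome measures as clinician-administered scales. They are the ratings for which a blinded assessor matters most, because the rater exercises judgement. The assessor forms that judgement from two conversations, and the preventive step covers one of them. An informant who mentions the mindfulness group while describing the participant's mood unblinds the assessor before the rating is complete.

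The carer QoL-AD raises a different problem. It is the carer's own report, so a blind assessor does not make it a blinded measure.

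The Statistical analyses section uses the clinical outcomes to estimate likely effect sizes with 95% confidence intervals and plans a power calculation for the future RCT. If those estimates rest on ratings that were not reliably blind, the planning of the next trial inherits the weakness.

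**Working it through.** The plan gives no figure on this point to reproduce, and no rate of disclosure from which a bias could be calculated. The check is a comparison of sections.

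1. **Who must be blind.** The outcome assessor (Design).
2. **Who is told not to disclose.** Participants. The Design section names no carer, relative or staff member as a recipient of the reminder, and no other section adds one.
3. **Who else speaks to the assessor.** A staff or family informant (Carer measures). The text gives this interview to the assessor, not to a separate interviewer.
4. **Whether those answers reach the rating.** Yes. They are combined with the participant interview to complete the listed scales, which include the CSDD and RAID.
5. **Whether the informant is likely to know the arm.** This is inferred, not stated. For family the inference is strong. The Intervention section has participants in MBCT practise with audio recordings on at least five days a week and fill in daily practice logs, which would be hard to miss at home. The Design section plans to interview carers of group attenders about practice and change at home, which presupposes that they know of attendance. The recruitment and delivery section puts those interviews within three weeks of the groups ending, and the Outcome measures section has assessments after the intervention and again six months later. For staff the inference is weaker, because their role and any contact with the groups are not described.
6. **When the exposure arises.** Baseline assessment precedes randomisation, so only the follow-up visits are affected.
7. **What the arm guess does.** It can pick up unblinding from any source, informants included. It is made after the assessment, so it cannot protect that rating, and as described it does not record how the assessor came to know.

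Two routes need to be kept apart. Disclosure from informant to assessor affects the CSDD and RAID and can be reduced by a reminder. The informant's own expectations can colour their answers on all three measures, and no reminder removes that.

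**The case against.** The strongest objection is that a journal article condenses the protocol, and that instructions to assessors and form fields belong in fuller documents. That would answer a complaint that blinding procedures are missing. It does not answer this one. The article states the safeguard, names its recipients and separately describes an informant interview that the safeguard, as worded, does not reach.

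The second objection is that the plan does check blinding, through the arm guess. That is correct, and it would be wrong to say the participant reminder is the only blinding measure. It is the only preventive one at the visit.

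The third is proportion. The primary outcomes are recruitment, retention, adverse events and acceptability, and they do not depend on these ratings. No hypothesis testing is planned. With 16 per arm, the 95% interval for a standardised difference has a half-width of about 1.96 × √(2/16) = 0.69 SD, so imprecision will be large whatever happens to blinding. This stands and limits the severity. It does not remove the point, since an interval reflects sampling error and does not reveal a systematic shift.

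A reader might also infer more than the documents support:

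- **That a group facilitator will act as informant.** The text does not exclude it, but nowhere says it will happen or is likely.
- **That informants will change between visits.** Nothing says so.
- **That carers will witness the weekly support calls.** The Intervention section describes a call from a team member and mentions no carer.
- **That the bias can be sized, or must favour MBCT.** Assuming that 10% to 30% of immediate-arm informants disclose and that each disclosed rating shifts by 0.3 to 0.5 SD gives 0.10 × 0.3 = 0.03 to 0.30 × 0.5 = 0.15 SD. Every input there is assumed, so the result is not evidence. A shift towards MBCT is plausible, not established.

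**Conclusion.** The point holds as a gap in how the blinding safeguard is worded. The assessor interviews an informant who may well know the allocation and uses the answers in the CSDD and RAID, while only the participant is asked not to disclose. The arm guess detects loss of blinding afterwards but neither prevents it nor traces it.

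The conclusion rests on one inference, that informants often know the arm. It is well supported for family and weaker for staff. No size of bias is claimed, because the documents give no disclosure rate.

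Severity is minor to moderate. The feasibility conclusions on recruitment and retention are untouched. The effect is on how far the effect-size estimates can be trusted when the future RCT is planned. The article does not say which estimate will enter the power calculation, so the link to that sample size is possible rather than certain.

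**What to change.** In the Design section, extend the non-disclosure reminder to the staff or family informant before each follow-up visit.

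In the Carer measures section:

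- Do not use anyone who delivered the MBCT groups or made the support calls as the informant where another is available.
- Record the informant's role and any disclosure of allocation, so that a correct arm guess can be traced to a source.
- Describe the carer QoL-AD as not blinded, since a reminder cannot remove the carer's own expectations.

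The cost is a few lines of wording and one form field. The downside is that a less familiar informant will occasionally have to be used. In return, this feasibility trial would also show whether assessor blinding can be maintained with informant-based scales in the full RCT.

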The two clinical researchers aim to run two MBCT groups each, two at each site with approximately eight participants in each. The clinicians running the groups will monitor the feasibility of recruiting participants (for both IA and DAC groups) within the given time frame. This will ideally include 16 participants in each of the two locations.

At least two clinicians have been allocated to each of the groups so that in the event that a group facilitator is unavailable (e.g. leave, sickness), the remaining facilitator will run the group alongside co-facilitators.

The qualitative interviews with participants and their carers will be conducted within 3 weeks of the groups having been completed. As such, it is expected that all data collection will have been completed by December 2016.

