### Outcome measures

The primary outcome measures will assess feasibility outcomes and be:Recruitment rate (incorporating willingness of patients to be randomised and practicality of the MBCT intervention)The recruitment will be deemed feasible if it is possible to recruit the required 32 participants in the given time frame of 4 months (June 2016–September 2016).Retention rate (incorporating acceptability of the therapy)The attrition and retention rates will be assessed and defined as the number of sessions completed and people assessed at follow-up, including details of withdrawals. We will judge an acceptable completion rate as 55% of people completing four or more of the eight course sessions and a follow-up completion rate of at least 75%.Incidence of adverse eventsWe will be collecting details of any adverse events that might arouse from evaluations and or delivery of the intervention.Acceptability of the developed MBCT programmeWe will be using qualitative interviews in order to further assess the acceptability and perceptions of the users in relation to the intervention, and its results will inform the final design of the intervention and consider this intervention as acceptable for this client group.Acceptability of the clinical outcome measures for inclusion in the studyWe will be assessing the feasibility of the outcome measures by exploring the missing data from the measures used and examine the inclusion exclusion rates from the recruitment process, and this will inform future RCT trial design.

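### The interviews behind the primary acceptability outcome are offered only to people who attended the group, with no provision to hear from those who never start or who stop early

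*Protocol article*

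**What the plan says.** The Outcome measures section introduces its list of primary outcomes with "The primary outcome measures will assess feasibility outcomes". Acceptability of the MBCT programme is a separate item on that list. The method given under it is qualitative interviews, and the section says that "its results will inform the final design of the intervention and consider this intervention as acceptable for this client group".

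The Design section says who is interviewed. In general terms, "a progress evaluation will be carried out by interviewing participants taking part in the groups". More specifically, "participants that attended the group will be invited to a semi-structured interview after the group". On numbers: "Approximately 10–12 interviews with group participants and family caregivers will be conducted". The carers' role is also described: "Carers of participants will be invited to further examine whether potential benefits of the MBCT intervention were generalised".

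The Procedure section fixes the timing: the interviews "will be conducted within 3 weeks of the groups having been completed". The same section says that a person who shows discomfort with the assessments or the groups will be discontinued.

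Acceptability also appears in a second primary outcome, "Retention rate (incorporating acceptability of the therapy", which counts sessions completed and people followed up and records details about those who withdraw. Its thresholds are 55% of people completing at least four of the eight sessions, and 75% followed up.

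**The concern.** An interview study of acceptability needs to reach people for whom the programme did not work as well as those who stayed. Here the invitation is tied to attendance, and the timing is tied to the end of the course. Someone allocated to MBCT who never came is outside the frame. Someone who left after one or two sessions may be inside it, but no one is tasked with finding that person, and the interview would come only after the eight-week course had ended. In people with dementia, recall of why they left may be poor by then. The carers, who could fill the gap, are asked about the spread of benefits; burden and reasons for stopping are not a stated aim.

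What is at stake is the redesign of the intervention before a full trial. The interviews are the stated source of in-depth information for it. If they come mainly from people who stayed, barriers that led others to leave or not to start may be carried into the larger trial.

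**Working it through.** The protocol gives no figure for this point, so there is nothing to reproduce. The check has two parts: who falls within the stated frame, and how large the group at risk of being missed could be.

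**Who is covered**

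| Group | Invited to interview? | Captured elsewhere? |
|---|---|---|
| Attended most or all sessions | Yes | Retention |
| Attended at least once, then stopped or was discontinued | Not ruled out, since attendance has no stated minimum; no step to approach them | Retention and withdrawal details |
| Allocated to MBCT, never attended | No | Retention and withdrawal details |
| Carers | Yes, with a stated focus on benefits | Carer-rated scales |

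**How large the group could be**

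Inputs: 16 per arm and 32 in total (Target group and sample size); a 55% completion criterion (Outcome measures); about 10–12 interviews, shared with carers (Design).

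- Fewest completers that meet the criterion in the immediate-access arm: 0.55 × 16 = 8.8, rounded up to 9.
- Most non-completers that still meet it: 16 − 9 = 7, and 7/16 = 43.75%, or about 44%.
- If the criterion is applied to both arms once the delayed group is offered MBCT: 0.55 × 32 = 17.6, rounded up to 18; 32 − 18 = 14; 14/32 = 43.75%.

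These are the largest numbers compatible with the criterion, not expected rates. The split between people who attend no session and people who attend one to three is not given.

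**Interview places against that group**

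- Even if every interview were with a different participant, 10/32 = 31% to 12/32 = 38% of the sample would be heard. Because places are shared with carers, the share of participants is likely to be lower.
- Nine completers in the immediate-access arm, each with a carer, give 9 × 2 = 18 potential interviewees for 10–12 places. Completers and their carers could fill every place, and the plan would have been followed without one low attender being interviewed.

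The size of any resulting bias cannot be calculated. The interviews are to be analysed thematically, so they will yield no acceptability percentage to compare with a true value.

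**The case against.** The strongest reply is that acceptability does not rest on the interviews alone. The retention outcome explicitly incorporates it, has numerical thresholds and records details of withdrawals, so non-starters and early leavers pull those figures down. Willingness to be randomised is counted under recruitment. The interviews are described as a further assessment that supports the quantitative findings, and their stated aim is to learn what attending a mindfulness group is like, which a person who never came cannot report. Home-practice logs, weekly calls and adverse event records add information on burden. Finally, a journal article commonly leaves the selection of interviewees to a fuller document.

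Much of this stands. A reader might infer that people who found MBCT unacceptable, including all early leavers, are excluded by design. The protocol does not support that: it sets no minimum for having attended, so a person who came once and disliked it can be invited. Nor do the documents support the inference that the interviews will overstate acceptability by some amount; they may lean that way. One might also read the phrase about considering the intervention acceptable as a conclusion fixed in advance, but the sentence is awkwardly written and this is an editing matter.

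The reply does not dispose of the point. Retention shows how many leave; the article does not say what the withdrawal details will contain, and it assigns the shaping of the final intervention to the interviews. The invitation rule is not omitted detail: it is stated, and it is tied to attendance.

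**Conclusion.** The point holds as a limitation of the stated interview frame. For a primary acceptability outcome, the interviews are offered to attenders and held after the course. Never-attenders are outside the frame, and hearing from people who stop or are discontinued is left to chance. Up to 7 of 16 immediate-access participants (44%) could complete fewer than four sessions while completion was still judged acceptable, and the plan requires none of them to be interviewed.

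This rests on two readings: that attending means coming to at least one session, and that the 55% criterion is applied to all those allocated in an arm of 16. The direction of the selection, towards favourable views, is a reasonable expectation and not something the documents demonstrate. The recruitment and retention outcomes are unaffected. The change is a cheap improvement to the qualitative component.

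**What to change.** Keep the 10–12 interviews and change the sampling rule in the Design section:

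- Invite everyone who was offered MBCT, whatever their attendance, and sample purposively by number of sessions attended.
- Reserve about 3–4 places for people (or their carers) who did not start or who stopped before session four.
- Approach these people when they stop, and adjust the timing sentence in the Procedure section to allow it.
- Reword the acceptability outcome so that the interviews inform whether the intervention is acceptable.

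If this is not wanted, say what counts as having attended and limit the qualitative acceptability conclusion to attenders.

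The cost is a sampling sentence, a timing sentence and an invitation letter, with no extra interviews. The downside is that some who stopped will decline, and slightly fewer full attenders will be interviewed. Any approach to people who have stopped would have to stay within the consent and capacity provisions that the protocol already describes.
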